#### Data collection & analysis

The data will be analysed according to the following main aims:

1. To describe the longitudinal evolution of early neurobehavioural development in very preterm infants (<30 weeks’ GA), from birth to two years CA the mean and 95% confidence intervals (CI) for the neurobehavioural assessment will be presented by week up to 32 weeks’ gestation, then fortnightly from 32 weeks’ gestation to term equivalent age, as well as at 1 and 2 years corrected age. Data will be presented according to both gestational and chronological age. Trends over time (according to both chronological and gestational age) will be explored using a mixed effects regression model for each outcome fitted to the continuous age measurement with a fixed effect of time (age) and a random effect for individuals to allow for the repeated observations on each infant.

2. To explore whether the neurobehavioural trajectory varies according to MR findings at term, qualitative MRI variables of interest will be dichotomised into two distinct categories (moderate to severe vs. none or mild white matter injury). The mean (and 95% CI) scores for the neurobehavioural development outcomes at each time point (as described for aim 1) will be plotted separately for children within each category. The change in neurobehavioural development over time (according to both chronological and gestational age) will be modelled using separate mixed effect regression models for each of the neurodevelopmental scores with a fixed effect of time (age) an indicator for moderate-severe injury and an interaction between time and the injury indicator, to assess whether the effect of time is different in those with a moderate-severe injury compared with those with no or a mild injury. The association between early neurobehavioural development and quantitative MRI (e.g. volumes, diffusion, metabolites such as NAA and cho) will be analysed using linear (continuous outcomes) and logistic (binary impairment outcomes) fitting a separate regression model for each outcome and neurobehaviour time point (according to both chronological and gestational age).

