3. The validity of early neurobehavioural assessments from birth to term-equivalent age for predicting development at one and two years’ CA in very preterm children will be investigated using separate linear (continuous outcomes) and logistic (binary impairment outcomes) regression models for each neurobehavioural assessment time point according to chronological and gestational age and each outcome. Estimates of the regression coefficients and the R^2^ values (representing the proportion of variability in the outcome explained by the model) from these models will be compared with estimates from the same models using neurobehaviour at term equivalent age as the predictor to obtain an idea of the predictive ability of these early measurements compared with the measurements at term as used currently. Data from term-born controls will be used to provide a local-reference population for calculation of mild, moderate and severe developmental impairment (mild = more than 1 SD below the mean, moderate = more than 2 SD below the mean, severe = more than 3 SD below the mean on the Cognitive Composite Scale on the Bayley-III).

4. To examine symptoms of depression, anxiety, and post-traumatic stress in mothers and fathers of very preterm children at birth during the first two years of the child’s life compared with term-born controls, we will present means and 95% CI for each parental assessment at each time point. For each time point, the observation closest to the specified time for the completed week within +/− 3.5 days for weekly assessment and +/− 7 days for fortnightly assessments will be selected for each individual.

5. To examine the relationships between parental psychological wellbeing, parent and family factors, and very preterm children’s neurobehavioural development at birth, and later two year-old cognitive, motor and social-emotional developmental outcomes, we will fit separate linear regression models for each of the two year outcomes. Initially each parent and child factor will be explored using separate univariable models for each outcome before combining important factors into a single model for each outcome to assess independent predictors.

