### Sample size

A sample of 150 very preterm infants and 150 term-born controls was chosen based upon projected workload, the number of infants <30 weeks cared for each year at the Royal Women’s Hospital, and the expected consent rate for the study from families. A sample of 150 infants will enable us to estimate the mean of any neurobehavioural measure employed in this research at any time point to within +/−0.16 standard deviations (based on a 2-sided 95% confidence interval, Aim 1), and to identify correlations between observations as small as 0.2 (Aims 2 and 3), with 80% power (based on 5% significance).

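### The 80% power for correlations of 0.2 is attached to Aims 2 and 3 as a whole, but it fits only continuous outcomes with a one-sided 5% test and does not extend to the logistic models on impairment

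*Protocol article*

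**What the plan says.** The Sample size section makes two statements about the 150 preterm infants. The first concerns precision for Aim 1 and names its convention: "based on a 2-sided 95% confidence interval, Aim 1". The second concerns power. The sample should be able "to identify correlations between observations as small as 0.2 (Aims 2 and 3), with 80% power (based on 5% significance"). No sidedness is given for the second statement, and nothing restricts it to a type of outcome or model. No odds ratio, impairment rate or power for a binary outcome appears.

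The Data collection & analysis section puts binary outcomes into both aims. Under Aim 2, the association with quantitative MRI "will be analysed using linear (continuous outcomes) and logistic (binary impairment outcomes) fitting a separate regression model for each outcome and neurobehaviour time point". Under Aim 3, prediction of development at one and two years is studied "using separate linear (continuous outcomes) and logistic (binary impairment outcomes) regression models for each neurobehavioural assessment time point". Aim 3 also defines impairment on the Bayley-III cognitive composite relative to the term controls: "mild = more than 1 SD below the mean, moderate = more than 2 SD below the mean, severe = more than 3 SD below the mean".

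**The concern.** One figure, a correlation detectable with 80% power, stands for everything done under two main aims. Those aims include models for which a correlation between two continuous scores is not the effect measure. Cutting a continuous outcome into impaired and not impaired discards information, so the same underlying association is harder to detect. A reader would reasonably take the Sample size section to mean that the impairment analyses have the same sensitivity as the analyses of scores.

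The 80% also needs checking in its own right. The neighbouring precision statement is two-sided, and a reader would normally assume a two-sided 5% test for the correlation as well.

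At stake is how an imprecise or non-significant result is read, above all in Aim 3, where impairment is one of the outcomes to be predicted.

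**Working it through.** **Inputs from the protocol.** n = 150, r = 0.2, 80% power, 5% significance (Sample size). Linear and logistic models in Aims 2 and 3, and cuts at 1, 2 and 3 SD below the control mean in Aim 3 (Data collection & analysis).

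**Assumptions.** Normal scores, all 150 infants analysed, and an underlying correlation of 0.2 before dichotomising. The protocol gives no impairment rate, so a range is shown.

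**Step 1: the plan's own figure, continuous outcome.** By Fisher's z, power = Φ(atanh(r)·√(n − 3) − z_α). Here atanh(0.2) = 0.2027 and √147 = 12.124, with product 2.458.

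- One-sided 5%: Φ(2.458 − 1.645) = Φ(0.813) = 79.2%. The sample needed for 80% is ((1.645 + 0.842)/0.2027)² + 3, which rounds up to 154; a regression-slope formula gives about 151.
- Two-sided 5%: Φ(2.458 − 1.960) = Φ(0.498) = 69.1%. The sample needed for 80% is ((1.960 + 0.842)/0.2027)² + 3, or 194. The smallest r detectable with 80% power at n = 150 is tanh(2.802/12.124) = 0.227.

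Simulating the t test of r (40,000 runs) gave 79.3% one-sided and 69.4% two-sided. The stated 80% is therefore reproduced, approximately, only one-sided.

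**Step 2: the same association with a binary outcome.** If a normal score is cut so that a fraction p is impaired, the correlation becomes r_pb = r·φ(z_p)/√(p(1 − p)). The multiplier is largest at p = 50%, where it is 0.399/0.5 = 0.798. A correlation of 0.2 thus becomes 0.160 at most. Putting r_pb into the Step 1 formula gives:

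| Impaired (p) | Multiplier | r_pb | Two-sided power | One-sided power |
|---|---|---|---|---|
| 50% | 0.798 | 0.160 | 50% | 62% |
| 40% | 0.788 | 0.158 | 49% | 61% |
| 16% (15.9%) | 0.662 | 0.132 | 37% | 49% |
| 7% (6.7%) | 0.519 | 0.104 | 24% | 35% |
| 2.3% | 0.362 | 0.073 | 14% | 22% |

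The rates correspond to possible positions of the preterm mean. For instance, Φ(−1) = 15.9% is the 1 SD cut with no shift from controls, and Φ(−1.5) = 6.7% is the 2 SD cut with a preterm mean 0.5 SD lower.

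Simulated logistic regression (20,000 runs per prevalence, two-sided, Wald and likelihood-ratio tests) gave 49% and 51% at p = 50%, 36% and 38% at 16%, and 10% and 14% at 2.3%. A cruder approximation that treats the underlying scale as logistic gives up to 62% two-sided at p = 50%, still below 69%.

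**Step 3: what the logistic models can detect.** The log odds ratio per SD detectable with 80% power, two-sided 5%, is approximately b = 2.80/√(n·p(1 − p)).

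- p = 40%: 2.80/√36.0 = 0.467, odds ratio about 1.6.
- p = 16%: 2.80/√20.2 = 0.624, odds ratio about 1.9.
- p = 6.7%: 2.80/√9.35 = 0.916, odds ratio about 2.5.

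**The case against.** The strongest reply is that the protocol claims power for correlations and nothing else. It states no power for a logistic model, so no logistic figure can be false. That stands: the fault is an over-broad label, together with an unstated sidedness. A reader might infer that the protocol asserts 80% power for the impairment models; it does so only by attaching the figure to whole aims.

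Several further points on that side also stand.

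- Setting two-sided binary power against the stated 80% would exaggerate the loss, because that 80% is roughly a one-sided figure. The like-for-like comparisons are 69% against at most about 50% (two-sided), and 79% against at most 62% (one-sided).
- No impairment rate is given, so no single power range for the logistic models can be read from the protocol.
- The SD cuts are defined only in Aim 3 and only for the Bayley-III cognitive composite. Aim 2 states no cut for its binary outcomes and also contains mixed-effects models. The text does not say that a separate logistic model is fitted at each severity level.
- The sample was set by workload, infant numbers and expected consent, and Aim 3 compares coefficients and R² descriptively. Nothing says that a non-significant logistic result will be taken as evidence of no prediction; that is a risk for the reader, not a stated rule.

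One might also read 0.2 as the correlation observed with the binary outcome itself, for which power is about the same as in the continuous case. But that requires a stronger underlying association: 0.2/0.798 = 0.25 at 50% impairment and 0.2/0.662 = 0.30 at 16%. The figure would then mean different things for the two kinds of model.

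**Conclusion.** The point holds as a misattached and incompletely specified figure. For continuous outcomes with all 150 infants, the stated 80% is met only approximately and only one-sided (79%). Two-sided power is 69%, and the correlation detectable with 80% power is about 0.23. For the logistic models, an underlying correlation of 0.2 has at most about 50% power two-sided, or 62% one-sided, whatever the impairment rate.

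That ceiling rests on normal scores and complete data. The values at particular rates rest in addition on assumed rates and are illustrative. The MRI scan is optional and some infants may be lost to follow-up, so the analysed numbers may be lower and power lower still; the protocol gives no rates for either.

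A reader might go further and conclude that the logistic models should be demoted, restricted to one cut, or replaced by counts for severe impairment. The protocol does not support that as a correction. Linear models on continuous outcomes are already planned in both aims, and how to rank the two is a design preference.

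**What to change.** In the Sample size section:

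- State whether the 5% test is one-sided or two-sided.
- Limit the correlation statement to the linear models on continuous outcomes. If two-sided, give the corrected figure: 69% power at a correlation of 0.2, or 80% power at about 0.23.
- For the logistic models, add the odds ratio per SD detectable with 80% power at stated, assumed impairment rates. With 150 infants this is about 1.6 at 40%, 1.9 at 16% and 2.5 at 7%.

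This needs no new data, no additional infants and no change to the planned models or their order. The cost is a less favourable stated figure.

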### Aims

The main aims of this study are to:

1. Describe the evolution of early neurobehavioural development in infants <30 weeks from birth to two years’ CA compared with children born at term, and to explore how neurobehaviour is influenced by perinatal variables.

2. Explore the relationship between early neurobehavioural development and neonatal brain abnormalities (development and injury) at term using multi-modal MRI in infants <30 weeks at birth.

3. Investigate the predictive validity of neurobehavioural assessments during the early neonatal period for developmental outcomes at one and two years’ CA in infants <30 weeks at birth.

4. Examine symptoms of depression, anxiety, and post-traumatic stress in mothers and fathers of infants <30 weeks at birth and to describe changes in parental psychological wellbeing over the first two years of the child’s life compared with children born at term.

5. Examine parental psychological wellbeing, and parent and family factors during the neonatal period as predictors of development at one and two years’ CA in children born <30 weeks, and whether these relationships are similar in children born at term.

In addition, secondary aims of this study are to:

1. Explore whether neurobehavioural examinations in the preterm period relate to concurrent physiological status (i.e. heart rate and oxygen saturations) in infants <30 weeks at birth.

2. Describe the parenting beliefs and practices of parents of infants <30 weeks at birth across the first two years of the child’s life.

3. Examine whether parental psychological wellbeing from birth to one year CA is associated with the parent–child relationship and child development when the child is one and two years’ CA in infants <30 weeks at birth.

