#### Magnetic resonance

The MRI scan is not a compulsory component of the study and parents consenting to the study can choose for their baby not to have the MRI scan. For those who consent, MRI scans will be performed without anaesthesia or sedation, between 38–44 weeks’ GA on the same day as the term equivalent age neurobehavioural assessment. All scans will be performed at the Royal Children’s Hospital using the 3 T Siemens Magnetom Trio MRI scanner. The scanning session will take approximately 60 minutes. A full anatomic, functional, developmental and metabolic infant brain MRI study will be performed using the following sequences:

•**T2-weighted images:** Transverse Restore turbo spin echo imaging: Flip angle = 120, Repetition Time = 8910 ms, Echo Time = 152 ms, Field Of View = 192 × 192 mm, Matrix = 192 × 192, 1 mm [3] isotropic voxels.

•**T1-weighted images:** Transverse multi-planar reconstruction imaging with noise suppression: Flip angle = 9°, Repetition Time = 2100 ms, Echo Time = 3.39 ms, Field Of View = 192 × 192 mm, Matrix = 192 × 192, 1.0 mm [3] isotropic voxels.

•**Diffusion weighted imaging:** Transverse echo planar imaging: Repetition Time = 20400 ms, Echo Time =120 ms, Field Of View =173 × 173 mm, Matrix = 144 × 144, 1.2 mm [3] isotropic voxels, 45 gradient directions (range b = 100 to b = 1200s/mm [2]), 3 b = 0 s/mm [2].

•**Resting state functional connectivity MRI:** Transverse 2D echo planar imaging with prospective acquisition correction: Repetition Time = 2910 ms, Echo Time = 28 ms, flip angle = 90°, Field Of View = 151 × 151 mm, Matrix = 64 × 64, 2.4 mm [3] isotropic voxels.

•**Proton magnetic resonance spectroscopy:** Transverse spin echo chemical shift imaging: Repetition Time = 2000, Echo Time = 135, flip angle = 90°, scan resolution = 12 × 12, interpolated 16 × 16, field of view = 103 × 125 mm, voxel size = 10.4 × 8.6 × 15.0 mm.

The MRI scans will be qualitatively evaluated by two independent investigators who are blinded to the clinical neurobehavioural assessment, utilising an established scoring method for newborn infants [42]. This scoring system provides an overall measure of the presence and severity of white matter, cortical grey matter, deep grey matter and cerebellar abnormalities (recorded as normal, mild, moderate, or severe). Quantitative image analysis will involve the following image analyses:

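### The stated 80% power to detect a correlation of 0.2 with 150 infants holds only for a one-sided 5% test; a two-sided test has about 69% power, or 80% power at a correlation of about 0.23

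*Protocol article*

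**What the plan says.** The Sample size section first explains that 150 very preterm infants and 150 term controls were chosen on practical grounds: workload, the number of eligible infants cared for each year, and the expected consent rate. It then describes what that number delivers. For Aim 1 it gives a precision of ±0.16 standard deviations, "based on a 2-sided 95% confidence interval, Aim 1". For Aims 2 and 3 it says that the sample will serve "to identify correlations between observations as small as 0.2 (Aims 2 and 3), with 80% power (based on 5% significance"). The second statement carries no sidedness of its own.

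The Aims section limits both of these aims to the preterm group. Aim 2 concerns brain abnormalities "at term using multi-modal MRI in infants <30 weeks at birth", and Aim 3 concerns predictive validity "for developmental outcomes at one and two years’ CA in infants <30 weeks at birth". The Magnetic resonance section adds that "The MRI scan is not a compulsory component of the study". The article gives no expected MRI uptake and no expected loss to follow-up.

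**The concern.** This is the only power figure in the article, and it covers two of the five main aims. Anyone who checks it under the usual convention of a two-sided 5% test finds that it does not reproduce. The shortfall is material: at a true correlation of 0.20 the chance of missing it is 31%, not 20%.

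The article's interest lies in whether assessments made before term relate to MRI findings and to later development. Such associations may be modest, so the smallest correlation that the study can reliably detect is what a reader needs to know when judging a null result. Stating 0.2 where the two-sided value is 0.23 makes the study look more sensitive than it is.

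**Working it through.** **Inputs**

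- n = 150 very preterm infants (Sample size). The controls do not enter, because the Aims section restricts Aims 2 and 3 to infants born before 30 weeks.
- r = 0.2, power 80%, significance 5%, sidedness not stated (Sample size).
- Normal quantiles: 1.960 (two-sided 5%), 1.645 (one-sided 5%), 0.842 (80% power).

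**Formulas (Fisher z)**

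- Power = Φ(atanh(r)·√(n − 3) − z_crit)
- Required n = ((z_crit + 0.842) / atanh(r))² + 3
- Smallest detectable r at 80% power = tanh((z_crit + 0.842) / √(n − 3))

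**Step 1: the other figure in the same sentence.** The half-width of a two-sided 95% interval is 1.96/√150 = 0.160 standard deviations. The Aim 1 precision of ±0.16 is correct.

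**Step 2: reproduce the stated 80%.** atanh(0.2) = 0.2027 and √147 = 12.124, so the product is 2.458.

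- One-sided 5%: Φ(2.458 − 1.645) = Φ(0.813) = 79.2%. This matches the stated 80%.
- Required n, one-sided: (2.4865/0.2027)² + 3 = 153.4, so 154.
- Detectable r at n = 150, one-sided: tanh(2.4865/12.124) = 0.202.

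**Step 3: the two-sided test.**

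- Power: Φ(2.458 − 1.960) = Φ(0.498) = 69.1%.
- Required n: (2.8016/0.2027)² + 3 = 193.97, so 194.
- Detectable r at n = 150: tanh(2.8016/12.124) = 0.227.

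**Step 4: is the result an artefact of the approximation?** It is not.

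| Method, n = 150, r = 0.2 | One-sided 5% | Two-sided 5% |
|---|---|---|
| Fisher z | 79.2% | 69.1% |
| Noncentral t | 80.1% | 70.0% |
| Simulation (50,000 bivariate normal samples) | 79.7% | 69.5% |

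**Step 5: could the controls explain it?** Pooling all 300 infants would give about 94% two-sided. That does not match 80% either, and the aims exclude the controls.

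**Step 6: fewer than 150 analysable infants (illustration only).** The article gives no MRI uptake or retention rate. The values of n in the last two rows are therefore assumptions. All rows use a two-sided 5% test.

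| n analysed | Power at r = 0.20 | Detectable r at 80% power |
|---|---|---|
| 150 | 69% | 0.227 |
| 120 (assumed) | 59% | tanh(2.8016/√117) = 0.25 |
| 100 (assumed) | 51% | tanh(2.8016/√97) = 0.28 |

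**The case against.** The strongest reply is that the article never says the correlation test is two-sided. The two-sided qualifier sits inside a bracket about the Aim 1 interval, and at one-sided 5% the printed figure is right. This stands as far as it goes. A reader might infer that the 80% is an arithmetical error, but the text does not prove that. What it shows is a figure that is true under one reading and false under the conventional one. The one-sided reading has no support elsewhere, though: the planned summaries use 95% confidence intervals, no one-sided test is announced, and neither aim names a direction for any score or MRI measure.

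A second reply is that 0.227 prints as 0.2 to one decimal. This is weak. The sentence presents 0.2 as the lower limit of what can be detected, so rounding down overstates sensitivity, and the same sentence gives the Aim 1 precision to two decimals.

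A third reply is that the sentence describes what 150 infants would give and makes no claim that 150 will have MRI or two-year data. That is fair. A reader might infer from the optional scan that Aim 2 is underpowered by a known amount, but without rates the document cannot support any such figure. A missing allowance for losses is also something that a condensed article may leave to the full protocol.

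Finally, Aims 2 and 3 are largely exploratory. Aim 3 compares regression coefficients and R² with those for the term-age assessment and sets no decision rule based on significance. Parts of both aims use mixed or logistic models, whose power a simple correlation does not describe. This stands, and it limits the consequence. The article nowhere says that a non-significant result will be read as excluding a correlation of 0.2.

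**Conclusion.** The point holds in this form: the sidedness of the test is unstated, and 80% power at a correlation of 0.2 with 150 infants is obtained only one-sided, which nothing in the article supports. Under two-sided 5% testing, power is about 69% (69% to 70% by method), the smallest correlation detectable with 80% power is about 0.23, and 0.20 would need 194 infants (154 one-sided). These figures assume one simple correlation, roughly bivariate normal data, and complete data on all 150 preterm infants.

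A reader might also conclude that the sample is too small and must grow. The document does not support that: the number was fixed on practical grounds, and the power sentence describes it without having determined it. The weight is moderate. The statement of what the study can detect should be corrected, but no design element depends on it.

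**What to change.** Replace the correlation part of the Sample size sentence with wording such as: *150 infants give 80% power (two-sided 5%) to detect correlations of about 0.23 or larger; power for a correlation of 0.20 is about 69%. These figures assume complete data on all 150 infants.*

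If a one-sided test was in fact intended, say so and justify a direction for each association.

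It would help to add the detectable correlation at the numbers that the investigators expect to have MRI (Aim 2) and follow-up (Aim 3), using their own rates. The values of 0.25 at 120 and 0.28 at 100 show the scale only.

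The cost is a change of wording and a slightly less favourable stated figure. No extra infants are needed, and no analysis or outcome changes.
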